### Sample size

Computation of a minimum required sample size is not statistically feasible for this study based on the observation of perceived QoL and psychological data taking into account the possible occurrence of RS. Indeed, the concept of RS is complex and novel in this disease and we have no preliminary data or any clear expectation for the results. The sample size will therefore be driven by the inclusion capacities of each center involved in the PreKiT-QoL study. Based on the extraction of the DIVAT data bank of the recipients transplanted between 2010 and 2012, one can expect that at least 130 recipients with preemptive transplantation (case) can be included during the four years inclusion period of the protocol. For each case, two control recipients who have experienced a pre-transplant dialysis period of less than 36 months will be included matched on gender, transplant center, and type of donor. A total of 390 patients will be included. This ratio 1:2 has been chosen to increase the sample size and the statistical power, the main expected limitation being the inclusion of patients receiving preemptive transplantation.

### Statistical analysis

Recipients will be described according to both groups, PPT and PDT. Such descriptive analyses will be performed on the main socio-demographic and clinical variables, either related to the recipient (except for the gender which is a matched between both groups), the donor or the transplantation. Categorical variables will be compared using Mac Nemar Chi2 tests for matched data. Continuous variables will be compared using a Student’s t-tests for paired data. This step will be important to assess the heterogeneity of the two populations and to identify possible confounding factors.

Structural equation models (SEM) and models coming from Item Response Theory (IRT) will be used to analyze changes in QoL and psychological dimensions (subjective well-being, perceived anxiety and depressive disorders, perceived stress) including the detection of response shift (RS) occurrence and its adjustment in the analyses, where appropriate, to estimate true changes. SEM and IRT will be used as complementary methods since SEM is appropriate for detecting RS at the dimension level (e.g. the “Physical Health” dimension of the RetransQoL) and IRT is appropriate for detecting RS at the item level within a dimension (e.g. the item “You are as well as anyone else” in the “Physical Health” dimension of the RetransQoL). SEM models [36] often include variables that are not directly observed (latent variables corresponding to QoL dimensions for instance) and possible links between these and the observed variables (observed scores for each QoL dimension). IRT models belong to the family of generalized linear random effects models [37]. They describe the probability of responding to each response category of a given item as a function of the latent variable one is trying to measure (patient’s “true QoL”) taking into account the psychometric characteristics of the scale through the questionnaire’s items parameters. Identification of RS and “true change” estimation (change in the subjective criterion being studied taking RS into account) will be performed in the following way: SEM analyses will follow the iterative algorithm developed by Oort [38] and IRT analyses will be done using a specific iterative algorithm called the RespOnse Shift ALgorithm in Item response theory (ROSALI) that has been recently developed [39].

Change in coping strategies and in post-traumatic growth will be measured at 6 and 24 months after transplantation and assessed using linear mixed models [40]. The GFR will be measured at hospital discharge, and 3, 6, 12, and 24 months post-transplantation and estimated using the MDRD formula [33]. A linear mixed model will also be used to handle these longitudinal measurements. Three explicative variables will be systematically taken into account: post-transplantation time, preemptive transplantation (yes/no) and the interaction between them. According to the non-linear relationship between the post-transplantation time and the GFR evolution [41], two slopes will be modeled with a breakpoint at 6 months. For all linear mixed models, random terms will be included on the intercept, on the slopes or both. Univariate (p < 0.2) and multivariate (p < 0.05) analyses will be performed in order to take into account possible confounding factors. The daily proteinuria will be measured at hospital discharge, and 3, 6, 12 and 24 months post-transplantation. This random variable is not Gaussian. A Gamma distribution is more appropriate but since a generalized linear models with such an inverse function as canonical link function will be difficult to interpret, the proteinuria will be divided into two classes for analysis: ≤0.5 g/24 h or >0.5 g/24 h. A logistic model with random effects will therefore be used [40]. The KTFS is a score that is computed at one year. The mean score at one year will be compared using a Student’s t-tests for paired data between the PPT and PDT groups.

The statistical significance level will be set at 5 % (type I error).

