**Methods/Design:**

Adult patients with a pre-emptive transplantation (n = 130) will be prospectively included along with a control group of patients with a pre-transplant dialysis period < 36 months (n = 260). Only first and single kidney transplantation will be considered. Endpoints include: comparison of change between groups in QoL, anxiety and depressive disorders, perceived stress, taking into account response shift. These criteria will be evaluated every 6 months prior to surgery, at hospital discharge, at three and six months, one and two years after transplantation.

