## Discussion

The main assumption of our study is that preemptive kidney transplant recipients, who generally present a better level of health than patients undergoing dialysis, might although have a lower perceived quality of life and have more difficulties in adapting themselves to their new status. In contrast with the increasing number of studies in cancer, exploration of response shift has, to our knowledge, never been done in the context of ESRD despite its relevance in this disease, particularly in the context of preemptive transplantation. Our study will give more insight on the adjustment processes at hand in preemptive patients compared with patients with a quite short period under dialysis. Thanks to this knowledge, it might then be useful to organize a therapeutic educational program and psychological support specifically adapted for these preemptive patients before and following the transplant surgery. Exploration of the expectations of patients regarding transplantation could help personalize the specific aims of educational programs. It could increase the level of preparedness for transplantation and a better acceptance of its consequences. This point would be of major importance to prevent bad adherence to treatment if our results show that preemptive patients “regret” being transplanted because they are possibly not enough prepared to this new health status.

From a methodological point of view, the main limitation of our study may be the possible lack of comparability of the two groups that will be compared (PPT and PDT) despite matching on gender, center, and type of donor. To minimize this issue, all the statistical analyses, including all response shift analyses, will try to take into account confounding factors.

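### McNemar and paired t-tests are named for a 1:2 matched design without saying how the second control enters, and the KTFS comparison adjusts for nothing beyond the matching factors

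*Protocol article*

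**What the plan says.** The Sample size section of the protocol article sets individual matching: "For each case, two control recipients who have experienced a pre-transplant dialysis period of less than 36 months will be included matched on gender", and also on transplant centre and donor type. It expects that "at least 130 recipients with preemptive transplantation (case) can be included", for a total of 390. The reason for two controls is explicit: "This ratio 1:2 has been chosen to increase the sample size and the statistical power".

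The Statistical analysis section then says "Categorical variables will be compared using Mac Nemar Chi2 tests for matched data" and assigns the paired Student t-test to continuous variables. It gives these comparisons two purposes: to judge how far the groups differ and to help find confounders. Later in the same section, KTFS, a secondary outcome, is handled in the same way: "The mean score at one year will be compared using" a paired Student t-test between the two groups. No covariates are mentioned for it.

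The Discussion names possible non-comparability of the groups as the main limitation and responds that "all the statistical analyses, including all response shift analyses, will try to take into account confounding factors".

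**The concern.** In standard form, McNemar's test and the paired t-test both work on one-to-one pairs, and 130 case values cannot be paired one-to-one with 260 control values. The article does not say how the second control enters. McNemar's standard form is also limited to binary variables, yet the article applies it to categorical variables without restriction. Table 1 includes initial disease, which has several categories.

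Three things are at stake.

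- **Error rate.** One way of forming pairs makes the standard errors too small, so the comparability tests would flag too many differences and the KTFS test would be too liberal.
- **Efficiency.** Another way discards 130 controls, and with them the gain for which the 1:2 ratio was chosen.
- **Confounding of KTFS.** The groups are not randomised, and a plain paired t-test controls only for gender, centre and donor type.

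**Working it through.** **Inputs from the protocol article.** There are 130 cases, two controls per case and a 5% significance level. Sidedness is not stated; two-sided is assumed here.

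**Reproducing the plan's figure.** 130 × (1 + 2) = 390, which equals the stated total, so the 1:2 structure is not in doubt. There is no power calculation to reproduce, because the sample size is set by recruitment capacity.

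**Assumptions not in the document.** Outcome variance s² is equal in cases and controls, and correlation ρ is the same for every pair of patients within a matched set.

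**Case minus the mean of its two controls (130 differences).**
Variance of the estimated group difference = (1 + 1/2)·s²(1 − ρ)/130 = 1.5·s²(1 − ρ)/130.

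**Each case entered twice (260 pairs treated as independent).** The point estimate is the same as above, so its true variance is still 1.5·s²(1 − ρ)/130. The test takes it to be 2·s²(1 − ρ)/260 = 1·s²(1 − ρ)/130.
- Ratio of assumed to true standard error = √(1/1.5) = √0.667 = 0.816. The factor (1 − ρ) cancels, so ρ does not matter under the stated assumptions.
- Type I error = 2·[1 − Φ(1.96 × 0.816)] = 2·[1 − Φ(1.60)] = 0.110.

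**One control dropped per case (130 pairs, 260 of 390 patients).** Variance = 2·s²(1 − ρ)/130.
- Ratio to the 1:2 analysis = 2/1.5 = 1.33, so the variance rises by 33%.
- The standard error rises by √1.33 − 1 = 15%.
- Relative efficiency is 0.75.

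**Simulation check.** This used 20,000 replicates of 130 sets and a two-sided 5% test. The 0.25 SD difference used for power is an assumption.

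| Continuous variable | ρ = 0 | ρ = 0.1 | ρ = 0.3 | ρ = 0.5 |
|---|---|---|---|---|
| Type I error, case minus control mean | 0.048 | 0.052 | 0.052 | 0.051 |
| Type I error, case entered twice | 0.110 | 0.113 | 0.113 | 0.109 |
| Type I error, one control dropped | 0.048 | 0.051 | 0.050 | 0.049 |
| Power at 0.25 SD, case minus control mean | 0.63 | 0.67 | 0.79 | 0.91 |
| Power at 0.25 SD, one control dropped | 0.51 | 0.56 | 0.67 | 0.81 |

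For a binary variable, with a random set effect of SD 0 or 1 on the logit scale (assumed), McNemar with each case entered twice rejected in 0.110 and 0.108 of null replicates. A Mantel-Haenszel test on the 1:2 sets rejected in 0.049 of replicates in both settings.

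**KTFS and confounding.** In the Statistical analysis section, covariate selection (univariate p < 0.2, multivariate p < 0.05) is described with the linear mixed models. The KTFS sentence comes later and names only a two-group test, which has no place for covariates. Set beside the intention in the Discussion, KTFS is left with adjustment for the three matching factors and nothing else.

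**The case against.** The strongest defence is that a valid paired t-test does exist for this design: subtract the mean of the two controls from the case value and test the 130 differences. It uses all 390 patients, holds the 5% level and is still a Student t-test for paired data. McNemar likewise has a Mantel-Haenszel extension to several controls, and multi-category extensions exist. A condensed article may leave such detail to an analysis plan.

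Much of this stands. A reader might infer that the named tests cannot be computed correctly at all. For continuous variables and KTFS the document does not support that, because a valid reading exists and is merely unstated. A reader might also take the 11% as the trial's actual error rate. It applies only if cases are entered twice, and the article nowhere says they will be.

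A reader might see a flat contradiction between the KTFS test and the Discussion. The Discussion only says the analyses will try to address confounding, and matching already handles gender, centre and donor type. Missing one-year scores do not make the approach collapse either: a set can still contribute with its case and one control, and the article gives no figure for KTFS availability.

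What does not fall is the basic mismatch. The article names specific tests, and as named they do not fit the matching it specifies. McNemar is the clearer case, because it fits neither two controls per case nor several categories. This is a method fixed badly, not detail left for later.

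**Conclusion.** The point holds in limited form. The tests named are one-to-one tests for a one-to-two design, with no statement of how the second control is used, and McNemar is applied beyond binary variables.

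The size depends on the analyst's choice. Type I error is about 11% if cases are entered twice, assuming equal variances and a common within-set correlation. The variance is 33% higher if one control per case is dropped. There is no loss if the case is compared with the mean of its two controls. The plan should not leave that choice open until the data are in hand. The KTFS comparison is also adjusted for nothing beyond the matching factors, which sits poorly with the stated intention for all analyses.

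A reader might extend this to the main results, but the document does not support that. The primary quality-of-life outcome uses structural equation and item response models. GFR, coping, post-traumatic growth and proteinuria use mixed or random-effects models, and the mixed models come with their own covariate selection step. Only the descriptive comparability tests and the secondary KTFS endpoint are affected. This should be fixed, but it does not threaten the primary analysis.

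**What to change.** Replace the three sentences that name these tests.

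- **Categorical variables:** conditional logistic regression, or a Cochran-Mantel-Haenszel test (the generalised form for more than two categories), stratified on the matched set.
- **Continuous variables:** a linear model with group as a fixed effect and a random intercept for the matched set, using all available patients, so that incomplete sets still contribute.
- **KTFS:** the same linear model, plus the non-matching confounders used for the other outcomes. Gender, centre and donor type need not be added, because they are constant within an exactly matched set.

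If the paired t-test is preferred for the descriptive continuous comparisons, it is enough to state that it is applied to the case value minus the mean of its controls, and how sets with a missing value are treated.

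The cost is a few reworded sentences and a few lines of code. The analysis file must carry a matched-set identifier, which individual matching already produces. No new patient data are needed.

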## Methods/Design

### Study design

The PreKit-QoL study is a prospective, multicenter, controlled study of quality of life, psychological adjustment process and medical outcomes of patients receiving a preemptive kidney transplant (PPT group) compared to a similar population of recipients after a dialysis period of less than three years (PDT group). The clinical and psychological data as well as the QoL questionnaires will be prospectively collected in the PPT and the PDT groups. Both groups will be matched regarding the recipient gender and the transplantation centers which are the two parameters differentially distributed between the two groups in our prospective cohort DIVAT (www.divat.fr). The type of donors (deceased or living) will be also matched between PDT and PPT. Since it is important to assess QoL before transplantation in order to evaluate response shift related to transplantation, the questionnaires will be collected for all patients waiting a first transplantation without dialysis or with a dialysis period of less than 36 months. Data will be collected at transplantation (sex, age, immunization, medical history, etc.). Other data that change over time, such as QoL, will also be collected every six months before transplantation, at hospital discharge, and 3, 6, 12 and 24 months after transplantation. The flowchart of the study is presented in Fig. 1.

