#### Secondary outcome measures

The following outcomes will be compared between PPT versus PDT:The change in generic QoL, subjective well-being, perceived anxiety and depressive disorders as well as perceived stress during follow-up (every 6 months before the surgery, at hospital discharge, 3, 6, 12, and 24 months post-transplantation) taking into account the possible occurrence of response shift. Generic QoL will be assessed with the SF-36 questionnaire. This questionnaire has the disadvantage of not being specific, and therefore less sensitive to specific changes in the health status of the recipient. However, it allows a comparison of the results to a reference population [25] and allows an easier comparison of the patients in different therapeutic frameworks (for example patients before and after transplantation). Subjective well-being, anxiety and depressive disorders, and perceived stress will be assessed using the satisfaction with life scale (SWLS) [26, 27], the Hospital Anxiety and Depression scale (HAD) [28, 29], and the Perceived Stress Scale (PSS) [30], respectively.Coping strategies (process of managing stressful circumstances) and post-traumatic growth (positive psychological change experienced as a result of the struggle with highly challenging life circumstances) at 6 and 24 months post-transplantation. Coping strategies and post-traumatic growth will be assessed using with the Brief Cope [31] and the Posttraumatic Growth Inventory (PTGI) [32], respectively.The post-transplantation graft and patient outcomes collected at hospital discharge, and 3, 6, 12 and 24-months post-transplantation: i) evolution of the Graft Filtration Rate (GFR) that will be estimated using the 4-variables MDRD formula [33], ii) evolution of the daily proteinuria that will be diagnosed by a simple dipstick test.The Kidney Transplant Failure Score at one year post-transplantation [34]. The KTFS is able to predict death-censored graft survival.The post-transplantation time to return to work, if appropriate.The compliance of patients will be assessed every six months prior to surgery, at hospital discharge, and at 3, 6, 12, and 24 months with the Girerd questionnaire [35].

In addition, other collected clinical data as well as variables related to the social status of the recipient are given in Table 1. The schedule of the study is presented in Table 2.

**Table 1 Tab1:** Clinical variables directly extracted from the DIVAT data bank

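### The linear mixed models for coping, post-traumatic growth and GFR choose confounders by p-value, which can leave bias in the between-group level effect and standard errors that ignore the selection

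*Protocol article*

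**What the plan says.** The protocol article, Statistical analysis, describes linear mixed models for coping, post-traumatic growth and GFR. After introducing the GFR model it names the terms that are always kept: "Three explicative variables will be systematically taken into account: post-transplantation time, preemptive transplantation (yes/no) and the interaction between them". It then says of random effects: "For all linear mixed models, random terms will be included on the intercept, on the slopes or both". The next sentence sets the confounder rule: "Univariate (p < 0.2) and multivariate (p < 0.05) analyses will be performed in order to take into account possible confounding factors". No covariate is forced in, and no random term for centre or matched set is named.

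Three other places bear on this:
- **Sample size.** Two controls per case "will be included matched on gender, transplant center, and type of donor". None of these three factors is among the terms that are always kept.
- **Note to Table 1.** Creatininemia is also collected before surgery, with adjustment for renal function as the stated purpose. It too is absent from the terms that are always kept.
- **Discussion.** Possible non-comparability of the groups despite matching is called the main limitation, and adjustment is the stated remedy. The same section says that preemptive recipients are generally in better health.

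**The concern.** Whether a variable confounds depends on its relation to both group and outcome, not on whether its coefficient reaches p < 0.05 in 390 patients. A rule based on outcome significance keeps the strong confounders and loses the weak ones. If several weak ones act in the same direction, their biases add up. The final model is then reported as though it had been fixed beforehand, so its standard error leaves out the uncertainty of the selection.

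This matters most for coping and post-traumatic growth. They are measured only at 6 and 24 months, with no pre-transplant value, so a between-group difference at those visits is a difference in level that only matching and adjustment protect. Age and medical history are not matched.

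**Working it through.** **The plan's own figure.** The article expects that "at least 130 recipients with preemptive transplantation (case) can be included", with two controls each: 130 × (1 + 2) = 390. This agrees with "A total of 390 patients will be included". No effect size, SD or power is given, so there is no power figure to reproduce.

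**Inputs from the document.** 130 and 260 patients; the 0.2 and 0.05 thresholds; group always kept; significance level 5% (taken as two-sided).

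**Assumptions.** No true group effect; residual SD 1; one outcome value per patient; backward elimination at the second step, since the article names no algorithm; K independent confounders, each with effect γ (SD per SD) and group imbalance δ (SD), all acting in one direction. 2,000 simulated trials per setting.

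**Selection step.** Confounding with no adjustment is K × γ × δ. Bias left is in SD; rates are false-positive rates.

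| K | γ | δ | K×γ×δ | Bias left | Share left | Rate, p-value rule | Rate, all kept |
|---|---|---|---|---|---|---|---|
| 6 | 0.10 | 0.30 | 0.180 | 0.053 | 29% | 10.2% | 4.9% |
| 6 | 0.10 | 0.30 (repeat) | 0.180 | 0.055 | 31% | 11.2% | 5.1% |
| 6 | 0.10 | 0.40 | 0.240 | 0.068 | 28% | 12.0% | 4.0% |
| 8 | 0.08 | 0.30 | 0.192 | 0.082 | 43% | 13.8% | 5.1% |
| 10 | 0.08 | 0.25 | 0.200 | 0.083 | 42% | 14.0% | 5.0% |
| 6 | 0.05 | 0.30 | 0.090 | 0.053 | 59% | 9.3% | 5.1% |
| 3* | 0.10 | 0.50 | 0.150 | 0.053 | 35% | 11.1% | 4.3% |
| 6** | 0.30 | 0.30 | 0.540 | 0.001 | 0% | 3.3% | 3.3% |

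\* Matching strata with SD 0.3, omitted from the model. \*\* Matching strata with SD 0.5, omitted; this is why both rates are below 5%.

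Simulation error is about ±1.3 points at 9.3% (1.96 × √(0.093 × 0.907/2000)) and ±1.5 at 14%.

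**Why the rate doubles.** In the repeated first setting about 3 of 6 confounders were kept. The mean reported standard error was 0.111 and the true SD of the estimate 0.124, so the ratio is 0.111/0.124 = 0.90. The rejection limit is 1.96 × 0.111 = 0.218. With mean 0.055 and SD 0.124, the upper tail is P(Z > (0.218 − 0.055)/0.124 = 1.31) = 9.5%. The lower tail is P(Z < −(0.218 + 0.055)/0.124 = −2.20) = 1.4%. The sum is 10.9%, against 11.2% simulated. Bias and a standard error that is too small both contribute.

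**Matching factors left out, sets complete.** Assume 28 strata (7 centres × 2 genders × 2 donor types) with between-stratum SD s. In complete 1:2 sets group is orthogonal to stratum, so the estimate is unbiased. The stratum variance goes into the residual, so the standard error is too large by about √(1 + s²).
- s = 0.5: √1.25 = 1.118. Simulated ratios of standard error to SD were 1.09-1.10, with false-positive rates of 3.2-3.4%.
- s = 0.3: √1.09 = 1.044. One run of 3,000 gave 1.087, but the model with strata gave 1.043 in the same run, so the net excess is 1.087/1.043 = 1.042.

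**Both together** (K = 6, γ = 0.10, δ = 0.30, s = 0.5): bias 0.065, ratio 1.00, false-positive rate 8.6%. The standard-error effects cancel and the bias remains.

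**Sets broken unevenly.** With 20% average loss running in opposite directions across strata in the two groups (an extreme assumed pattern), omitting the strata gave bias of 0.087-0.140 SD and false-positive rates of 9.8-16.3%. With the strata in the model, bias was about 0 and the rate 4.7-4.9%.

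**Group-by-time interaction.** The four δ/γ settings (6, 0.10, 0.30), (6, 0.10, 0.40), (8, 0.08, 0.30) and (10, 0.08, 0.25) were run with five visits, complete data, linear time, and random intercept and slope (3,000 runs each; variance components assumed). With no adjustment at all, interaction bias was 0.000 to −0.003 and rejection 4.2-5.1%.

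**The case against.** **The study compares change, and change is protected.** This stands for confounders that shift only the level, when data are complete. It does not remove the point. The Secondary outcome measures section compares coping and post-traumatic growth between groups at 6 and 24 months, and there the level difference is of interest.

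**The assumed confounders are unfavourable.** Their number, common direction and imbalance have no source in the article. The Study design section says of gender and centre, both matched, "which are the two parameters differentially distributed between the two groups in our prospective cohort DIVAT". Strong confounders are all retained. So the sizes are conditional. But the Discussion itself expects residual non-comparability, and the direction of the error does not depend on the exact values.

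**Other text softens the rule.** The descriptive group comparison is also meant to identify possible confounders, and age and medical history are collected. That widens the list of candidates; the stated thresholds still decide which stay. How matching enters each model may be left to a fuller document, but the thresholds are fixed here.

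Three stronger readings are tempting and are not supported:
- **Unforced matching factors make standard errors too optimistic.** With complete sets the reverse is true. The article also does not say that these factors are candidates for elimination; it only omits them from the terms that are always kept.
- **The primary QoL result is affected.** The rule stands with the linear mixed models. The structural equation and item response analyses are given no p-value rule.
- **The KTFS comparison is affected.** It is a paired t-test with no selection step.

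**Conclusion.** The point holds for the linear mixed models of coping, post-traumatic growth and GFR. The p-value rule can leave residual confounding in the between-group level effect, together with a standard error that ignores selection (about 10% too small in the worked setting). With several weak confounders acting in one direction (0.05-0.10 SD per SD, imbalance 0.25-0.5 SD), bias is about 0.05-0.08 SD and the false-positive rate about 9-14% instead of 5%. With strong confounders (0.3 SD per SD) there is no bias. The interaction is at risk only if confounders alter the slope or drive dropout.

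Omitting the matching factors is a separate, milder matter. Standard errors are about 9-10% too large at a stratum SD of 0.5 (false-positive rate about 3%) and about 4% too large at 0.3. Bias arises only if loss breaks the sets unevenly.

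The simulations used one outcome value per patient, except for the interaction check, so the directions are firmer than the exact sizes.

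**What to change.** Replace the selection sentence in Statistical analysis with an adjustment set fixed in advance on subject-matter grounds, from variables already collected: pre-surgery creatininemia, recipient age, initial disease, diabetes, cardiovascular and cancer history, and donor age. Add covariate-by-time terms where a confounder could plausibly alter the slope, because main effects alone would not correct that. Force in gender, centre and donor type, or a matched-set effect.

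**Cost.** A change of wording and a few degrees of freedom. In the worked setting the reported standard error rises from 0.111 to 0.115 (0.115/0.111 = 1.04), while the true SD of the estimate falls from 0.124 to 0.115. If none of the covariates affects the outcome, the SD rises by about 6% (0.110 to 0.117).

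**Two cautions.** If the same set is carried into the random-effects logistic model for proteinuria, it may have to be smaller when events are few. And because preemptive patients by definition still have a functioning kidney, the overlap of pre-surgery creatininemia between the groups should be examined before the model relies on it.

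### One-to-one matched tests (McNemar, paired t-test) are named for a design with two controls per case, and the pair is not defined

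*Protocol article*

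**What the plan says.** The Sample size section of the protocol article expects that "at least 130 recipients with preemptive transplantation (case) can be included" over four years. It continues: "For each case, two control recipients who have experienced a pre-transplant dialysis period of less than 36 months will be included matched on gender", with transplant centre and donor type as the other matching factors. The total follows: "A total of 390 patients will be included". The reason given for the second control is explicit: "This ratio 1:2 has been chosen to increase the sample size and the statistical power".

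The Statistical analysis section then names the tests. For the descriptive comparison of the groups: "Categorical variables will be compared using Mac Nemar Chi2 tests for matched data". Continuous descriptive variables get a paired Student test. The same section compares the mean one-year KTFS by "t-tests for paired data between the PPT and PDT groups". KTFS is listed under Secondary outcome measures. The significance level is 5%; sidedness is not stated.

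The other outcomes with a named analysis use other methods. Quality of life and the psychological scales use structural equation and item response models. Coping, post-traumatic growth and graft filtration rate use linear mixed models. Proteinuria uses a logistic model with random effects.

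**The concern.** McNemar's test compares one binary observation on a case with one on its control. A paired t-test takes one difference per pair. The design supplies sets of three, and the article does not say what the pair is.

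For McNemar no direct reading works: with two controls per case it needs a 1:M extension. Table 1 also lists at least one variable with several categories (initial disease), which the ordinary 2x2 form cannot handle.

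For the t-test, an analyst who follows the text literally has three routes: keep one control per case, enter each case twice, or compare each case with the mean of its two controls. Only the third uses every patient and keeps the stated error rate. The first gives up the power for which the second control was recruited. The second treats 260 differences as independent although each case appears in two of them.

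At stake are the KTFS result and the descriptive comparison, which the Statistical analysis section says will help to identify confounders.

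**Working it through.** **Inputs from the protocol article.** 130 cases, two matched controls per case, 260 controls, 390 in total, significance level 5%.

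**Assumptions, not in the documents.** Two-sided testing; the same within-set SD *s* in cases and controls unless varied below; within-set correlation 0, 0.2 and 0.5; for binary variables, prevalence 0.1, 0.3 and 0.5.

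**1. The plan's own figure.** 130 x (1 + 2) = 390. It reproduces. No power calculation is given to reproduce.

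**2. All controls used at set level (case minus mean of its two controls).**
- Variance of the mean difference = s²/130 + s²/260 = 1.5 s²/130.
- Difference detectable with 80% power = (1.960 + 0.842) x sqrt(1.5/130) = 0.30 within-set SD.
- Simulated type I error of the paired t-test: 4.9% to 5.0%.
- For binary variables, the Mantel-Haenszel test for 1:2 sets: 4.4% to 5.2%.

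**3. One control per case dropped (130 pairs, 130 of 260 controls unused).**
- Variance = s²/130 + s²/130 = 2 s²/130.
- Relative efficiency = 1.5/2 = 75%; the standard error rises by sqrt(2/1.5) = 1.155, about 15%.
- Detectable difference with 80% power = 2.802 x sqrt(2/130) = 0.35 SD.
- Power for the effect that had 80% in step 2: Phi(0.301/sqrt(2/130) - 1.960) = Phi(0.466) = 68%. An effect that had 90% falls to 80%.
- Type I error stays near 5% (simulated 4.7% to 5.0% for the t-test and McNemar).

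**4. Each case entered twice (260 differences treated as independent).**
- Variance the test assumes = 2 s²/260 = s²/130. True variance = 1.5 s²/130. The set component cancels in each difference, so the within-set correlation does not matter.
- Type I error = 2 x [1 - Phi(1.960/sqrt(1.5))] = 2 x [1 - Phi(1.600)] = 10.95%.
- Simulated paired t-test: 10.8% to 11.1%. McNemar: 10.4% to 11.1% without continuity correction, 7.8% to 9.8% with it.
- Unequal variances: if the case variance is *v* times the control variance, true over assumed variance = (v + 0.5)/[(v + 1)/2]. For v = 0.5 this is 1.33 and the type I error 9.0%; for v = 2 it is 1.67 and 12.9%.

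The simulations used 130 sets and 10,000 replicates per scenario.

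**5. Missing KTFS, for illustration.** Assume 10% missing per patient, independently. Complete sets of three: 130 x 0.9³ = 95. Sets with the case and at least one control: 130 x 0.9 x (1 - 0.1²) = 130 x 0.9 x 0.99 = 116. Patients available to a model that does not require the whole set: 117 cases and 234 controls.

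**The case against.** The strongest reply is that the plan's words admit a correct analysis. A paired t-test of each case against the mean of its controls is still a t-test for paired data; it uses all 390 patients and holds 5%. This stands. It also rules out a stronger reading that a reader might infer: that the named tests must either discard half the controls or double-count the cases, with a type I error of 11%. The article states neither practice. The 11% belongs to one possible implementation and rests on equal variances.

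Two further inferences go too far. One is that any set with a missing member is lost: a set can stay if the case and one control are observed. The other is that p-values swing widely because several cases share a cell of centre, gender and donor type, so that the choice of set is arbitrary. With complete 1:2 sets and the mean of both controls, reshuffling sets within a cell cannot change the estimated difference, only its standard error. The estimate depends on the pairing when one control is dropped.

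It can also be said that the article is condensed and that an analysis plan may define the set-level computation. That has force for the t-test. It has less for McNemar, because the article names a test that does not fit the design it states; this is not a detail left out.

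Finally, the reach is narrow. Confounder selection in the mixed models has its own screen (p < 0.2, then p < 0.05), so it does not rest on the descriptive tests alone.

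**Conclusion.** The mismatch between the named tests and the 1:2 design is real. McNemar needs a 1:M extension, and a generalised form for multi-category variables. The paired t-test is sound with all patients only under a definition that the article does not give.

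The consequences are conditional on how the tests are carried out: no loss of patients from complete sets, and 5%, if the case is compared with the mean of its controls; 75% relative efficiency, with 80% power falling to about 68%, if one control is dropped, which cancels the stated reason for the ratio; about 11% type I error if cases are entered twice (about 9% to 13% for case-to-control variance ratios of 0.5 to 2). These figures assume two-sided testing and, apart from that last range, equal variances.

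Only the descriptive comparisons and the secondary KTFS outcome are touched. Nothing here bears on the primary quality-of-life analysis, the mixed-model outcomes or proteinuria. Severity is moderate to minor; the point should be corrected, but it does not threaten the study's main conclusion.

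**What to change.** Replace the named tests with methods that fit 1:2 matching and use every control.

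- **KTFS and continuous descriptive variables:** a linear model with group and the matching factors (centre, gender, donor type), or with a random set effect. Either also keeps patients from incomplete sets. A paired t-test of each case against the mean of its available controls is an acceptable alternative if the text says so and gives a rule for incomplete sets.
- **Categorical descriptive variables:** Mantel-Haenszel or conditional logistic regression on the matched sets, with a generalised form for variables with more than two categories.

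The cost is a change of wording in the Statistical analysis section and minor analysis work. No extra patients or data are needed.
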